#### Mixed-methods approach for summative evaluation

Based on the RE-AIM framework, we will use a mixed-methods approach with qualitative and quantitative data to summatively evaluate the MCCP (Table 2). For example, *reach* will be assessed quantitatively by comparing patient characteristics for patients who are referred to weight loss (i.e., exercise program, endocrine clinic, medications, endoscopic or surgical bariatric procedures) and/or hepatology within a given intervention PACT and those who are not within the same PACT. For *implementation*, we will use descriptive statistics to examine the average degree of fidelity to the intervention at the PACT level. We will also examine the association between the degree of fidelity and each binary outcome at 6 and 12 months.

**Table 2 Tab2:** RE-AIM elements and corresponding measures

RE-AIM Element	Corresponding Measure
Reach: *proportion and representativeness of individuals who participate in an intervention*	1) Characteristics of MASLD patients who are referred to weight loss in a given PACT compared with characteristics of all MASLD patients in a given PACT* 2) Characteristics of MASLD patients who are referred to hepatology in a given PACT compared with characteristics of all MASLD patients in a given PACT* 3) Differences between the intervention and control groups in the relationship between patient characteristics and each primary and secondary outcome at 6 months (see Effectiveness)
Effectiveness: *impact of an intervention on important outcomes*	1) Differences in the proportions of patients with MASLD diagnosis and risk stratification between intervention and control groups* 2) Differences in the proportions of patients with MASLD who are referred to a weight loss program within 6 months between intervention and control groups * 3) Differences in the proportions of patients with advanced MASLD who are referred to hepatology within 6 months between intervention and control groups* 4) Differences in the proportion of patients with MASLD who are referred to a weight loss program and start the program within 6 months between intervention and control groups* 5) Differences in the proportion of patients with advanced MASLD referred to hepatology and are seen in a hepatology clinic within 6 months between intervention and control groups*
Adoption: *proportion and representativeness of individuals who deliver the intervention*	1) Characteristics of PACTs participating in the study (make up of clinicians, number of clinicians in PACT) and differences between intervention and control groups in the relationship between PACT characteristics and each outcome at 6 months* 2) Differences among PACTs in frequency of referrals to weight loss and hepatology** 3) Barriers and facilitators to referral to weight loss and hepatology**
Implementation: *fidelity to elements of intervention*	1) Fidelity to MCCP intervention in terms of education/referral patterns and the relationship between degree of fidelity and each outcome at 6 months (based on documentation of checklist in CPRS)* 2) Adaptations of MCCP delivery by PACT members** 3) Time required to deliver MCCP as reported in interviews** 4) Patient experiences with PACT and providers using MCCP**
Maintenance: *extent to which intervention effects are sustained 6 or more months* (Examination of outcomes at 12 months)	1) Differences in the proportion of patients with MASLD who are NEWLY referred to weight loss program (within 6–12 months) between intervention and control groups* 2) Differences in the proportions of patients with advanced MASLD who are NEWLY referred to hepatology (6–12 months) between intervention and control groups* 3) Differences in the proportion of patients with MASLD who are referred to a weight loss program who actually start the program within 12 months between intervention and control groups 4) Differences in the proportion of patients with advanced MASLD referred to hepatology who actually see a hepatology clinic within 12 months between intervention and control groups

*quantitative measure

**qualitative measure

Qualitative data will include interviews with PCPs and nurses in both study groups to explore barriers and facilitators to the referral process and adaptations made while delivering the intervention (Table 3). Semi-directed content analysis will be used to analyze interview data [27]. This approach leverages pre-determined themes to structure analysis and allows new themes to emerge. RE-AIM framework will inform parent codes (e.g., adoption, implementation). Sub-codes (e.g., adoption: decision making) will allow for granular analysis and capture of various experiences.

**Table 3 Tab3:** PACT focus group questions for summative evaluation

Adoption
• *Intervention-arm:* Please share your initial perspective on MCCP. Did you have any specific concerns? Was there anyone in your PACT that seemed reluctant/resistant to any/all of the MASLD CCP intervention? • *Control arm:* Please share your initial perspective on MCCP. Did you have any specific concerns? • *Intervention-Arm:* About how long did it take to go from receiving notification about a patient at-risk for MASLD and referring them to weight loss/hepatology? What were some challenges encountered throughout this process?
Implementation
• What challenges were associated with the MCCP training? • About how long did it take to counsel/educate patients at-risk for MASLD? If/how did this impact the flow of the clinic? What were some challenges encountered throughout this process?

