### Outcomes

Patient-level clinical outcomes will be measured at six and 12 months following the delivery of the e-trigger results to the PACT. The primary outcome will be a composite dichotomous variable of making a new MASLD diagnosis and completing severity risk stratification of MASLD. Secondary outcomes include referral and receipt of hepatology specialty care for patients with MASLD and advanced fibrosis.

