#### Analysis plan for cluster-randomized trial

We will compare baseline outcome variables for demographics (e.g., age, gender, race), medications (e.g., diabetes, dyslipidemia, hypertension), comorbidities (i.e. metabolic conditions, other medical or mental health conditions), healthcare utilization (e.g., outpatient, inpatient encounters), and adherence to ambulatory care for the MCCP versus usual care participants using SAS Proc Mixed for continuous variables and SAS Proc Glimmix for categorical variables. We will also compare baseline PACT characteristics (e.g. number of clinician and provider mix) between the study groups. Variables that differ between the study groups will be included as covariates in subsequent outcome analyses. Outcome analyses will be performed at 6- and 12-months post-enrollment for both primary (i.e. dichotomous composite of a new MASLD diagnosis and risk stratification) and secondary (i.e. testing with Fibroscan, referral for hepatology/weight loss services) outcomes. Intention -to-Treat and Per-Protocol analyses will employ multilevel models that account for dependency of patients within PACTs. SAS Proc Glimmix will be used for each dichotomous outcome with study group (MCCP or usual care) as the main predictor and variables that differ between study group at baseline will be included as covariates.

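### Fidelity is defined partly by referral patterns and then related to referral outcomes, so for those outcomes a positive association is built in

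*Protocol article*

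**What the plan says.** **Predictor.** The Implementation row of Table 2 lists, as a quantitative measure, "Fidelity to MCCP intervention in terms of education/referral patterns and the relationship between degree of fidelity and each outcome at 6 months". The source is given as "based on documentation of checklist in CPRS". The text above the table (Mixed-methods approach for summative evaluation) says descriptive statistics will be used to "examine the average degree of fidelity to the intervention at the PACT level", and then adds: "We will also examine the association between the degree of fidelity and each binary outcome at 6 and 12 months".

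**Outcomes.** Referral appears as an outcome in several places:
- Outcomes section: "Secondary outcomes include referral and receipt of hepatology specialty care for patients with MASLD and advanced fibrosis".
- Analysis plan for the cluster-randomized trial, secondary outcomes: "testing with Fibroscan, referral for hepatology/weight loss services".
- Table 1: hepatology referral and weight loss referral, both taken from the CDW consult table at 6 and 12 months.
- Table 2, Effectiveness item 2: "Differences in the proportions of patients with MASLD who are referred to a weight loss program within 6 months between intervention and control groups". Item 3 is the matching measure for hepatology referral in advanced MASLD. Items 4 and 5 concern patients who are referred and then start the programme or are seen in clinic.

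The primary outcome contains no referral: "The primary outcome will be a composite dichotomous variable of making a new MASLD diagnosis and completing severity risk stratification of MASLD".

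**The concern.** The plan relates fidelity to every outcome and makes no exception for referral. A PACT that refers more patients scores higher on a measure built partly from referral patterns, and it also has a higher referral outcome. Some of the resulting association says nothing about whether delivering the training and patient education changes practice.

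Aim 3 is meant to identify what goes with effectiveness and to plan future implementation. A reader of the results could take a fidelity–referral association as evidence that fuller delivery yields more referrals, when part or all of it reflects referral being counted twice.

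**Working it through.** The article gives no figure for the fidelity–outcome association, so there is nothing to reproduce. The check has two parts.

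**1. Which outcomes share content with the fidelity measure**

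| Outcome | Overlap with referral patterns |
|---|---|
| Referral to weight loss within 6 months | By definition |
| Referral to hepatology within 6 months (advanced MASLD) | By definition |
| Programme start; hepatology visit | Partial: both depend on referral |
| New referrals at 6–12 months (Table 2, Maintenance) | Not necessarily; depends on the period over which fidelity is scored, which is not given |
| Fibroscan testing | None by definition |
| Primary outcome (diagnosis plus risk stratification) | None by definition |

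Nothing in the article exempts the referral outcomes, drops the referral component when they are analysed, or sets fidelity to be measured before the outcome window.

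**2. How large the built-in association could be**

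Input from the article: 8 PACTs per arm (Sample size).

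Assumptions, none stated in the article:
- Fidelity is one composite, F = w·R + (1 − w)·E, with R the referral part and E the education part.
- R and E are standardised, normal and independent across PACTs, so education has no true link to referral.
- The referral outcome equals R without error.
- The analysis is a two-sided 5% correlation test on 8 − 2 = 6 degrees of freedom.

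Expected correlation:

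corr(F, R) = w / √(w² + (1 − w)²)

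For example, at w = 0.25: 0.25 / √(0.0625 + 0.5625) = 0.25 / 0.791 = 0.32. At w = 0.5: 0.5 / √0.5 = 0.71.

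Simulated rejection rates across the range of w:

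| Referral weight w | Expected r | p < 0.05 |
|---|---|---|
| 0 | 0.00 | 5% |
| 0.10 | 0.11 | about 6% |
| 0.25 | 0.32 | about 12% |
| 0.33 | 0.44 | about 20% |
| 0.50 | 0.71 | about 56% |
| 0.75 | 0.95 | 99% |
| 1 | 1.00 | 100% |

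Runs of 20,000 and 200,000 replicates agree within about one percentage point at the weights common to both.

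Plausibility check: the critical correlation on 6 degrees of freedom is 2.447 / √(2.447² + 6) = 0.71. This equals the expected correlation at w = 0.5, so a rejection rate a little above one half is what one would expect there.

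For an outcome independent of both parts, the same simulation rejects in about 5% of runs at every w. The inflation is therefore confined to outcomes that share content with the score.

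**The case against.** **Referral is a legitimate fidelity element.** The pathway recommends referral, so whether PACTs make the recommended referrals is a fair measure of adherence. This stands. The problem lies only in using that element to explain referral outcomes.

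**The article does not describe a composite score.** It gives no items, weights or summation. The phrase could mean two components reported separately, or concordance with recommended referral rather than volume. Such detail may sit in a fuller document. This stands against any single figure for the size. It does not remove the overlap, because the article itself names referral patterns as part of fidelity and every outcome as the target.

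**Different data sources.** Fidelity comes from a CPRS checklist and referral outcomes from the CDW consult table. This reduces shared recording error, so the overlap may be less than perfect, but both sources record the same act.

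**Stronger readings that the text does not support.**
- A reader might infer that any finding of better outcomes with higher fidelity is built in, including for the primary outcome. The primary outcome and Fibroscan testing contain no referral element.
- A reader might infer that the plan commits to a correlation test on 8 PACTs, and so treat 56% as its error rate. PACT level is attached only to the descriptive step. No unit or significance test is given for the association, and the trial's outcome models are multilevel models of patients within PACTs. If fidelity were scored per patient, the overlap would be more direct, but these percentages would not describe it.
- A reader might infer that the effectiveness result is compromised. The comparison of MCCP with usual care does not use fidelity.

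**Conclusion.** The point holds in limited form. Followed as written, the plan puts the same referrals on both sides of the fidelity association for the 6-month referral outcomes, and partly so for programme start and hepatology visit.

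The direction follows from the definition if education and referral are unrelated. The size cannot be fixed from the article. Under the stated assumptions the false-positive rate can lie anywhere from the nominal 5% to 100%, depending on the referral weight; 0.71 and 56% belong to one assumed weight only.

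This is a flaw in one explanatory analysis within the summative evaluation, and worth correcting because that evaluation is to guide implementation.

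**What to change.** Keep referral adherence as a descriptive fidelity measure. For the association analysis, do one of the following:

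1. When the outcome is referral, programme start or hepatology visit, use a fidelity measure made only of delivery elements that share no item with the outcome, for example training and patient education from the CPRS checklist; or
2. Limit the fidelity–outcome association to outcomes that share no item with the fidelity measure.

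Label the association exploratory in either case. In the illustration, removing the referral part (w = 0) brings the expected correlation to 0 and the rejection rate to about 5%.

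The cost is a change to the Implementation row of Table 2, the matching sentence in the text and the checklist scoring. Under option 1 the measure has fewer items for those outcomes and so describes delivery less fully. Under option 2 there is no fidelity analysis for them. Sample size and the randomised comparison are unaffected.

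### Table 2 Maintenance items 3 and 4 count starts and visits from month 0 to month 12, so they cannot by themselves show that an effect lasted beyond month 6

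*Protocol article*

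**What the plan says.** All the measures are in Table 2, under the section on the mixed-methods summative evaluation.

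- **Maintenance, description:** the "extent to which intervention effects are sustained 6 or more months", followed by a note that outcomes are examined at 12 months.
- **Maintenance items 1 and 2:** these have a lower bound. Item 1 counts patients "NEWLY referred to weight loss program (within 6–12 months) between intervention and control groups". Item 2 counts "patients with advanced MASLD who are NEWLY referred to hepatology (6–12 months) between intervention and control groups".
- **Maintenance items 3 and 4:** these do not. Item 3 counts patients "who are referred to a weight loss program who actually start the program within 12 months between intervention and control groups". Item 4 counts "patients with advanced MASLD referred to hepatology who actually see a hepatology clinic within 12 months between intervention and control groups".
- **Effectiveness items 4 and 5:** these are the 6-month counterparts. Item 4 counts patients "who are referred to a weight loss program and start the program within 6 months". Item 5 counts those referred to hepatology and seen there by month 6.

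The Outcomes section gives a single time origin for the 6- and 12-month assessments: delivery of the e-trigger results to the PACT.

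**The concern.** With one time origin, every start or visit counted at 6 months is also a success at 12 months, whatever the patient or clinic does later. Items 3 and 4 therefore compare cumulative proportions over months 0 to 12. That is a different question from whether MCCP still had an effect after month 6. The contrast lies within one table cell: two of the four items are limited to months 6 to 12 and two are not.

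Maintenance feeds Aim 3, which plans future implementation. The education component lasts 2 to 3 weeks, so whether its effect persists is a real question. If the effect ended by month 6, items 3 and 4 could still show a difference between arms, and that difference would sit under the heading for sustained effects.

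**Working it through.** **Inputs.** The documents give no rates for programme starts or hepatology visits, and no power figure for the Maintenance items, so there is no stated figure to reproduce. The 7% versus 17% used below comes from the Sample size section, where it describes the primary outcome. It is borrowed only to illustrate. The values of h, the referral rates and the conversion rates are assumptions.

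**Reading A: all eligible patients in the denominator.** Let pC and pT be the proportions with a start (or visit) by month 6. Let h be the chance of a first event in months 6 to 12 among those without one, equal in both arms, so that there is no effect after month 6.

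- 12-month proportion in each arm: p + (1 − p)h
- 12-month difference: (pT − pC)(1 − h)

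| h | Usual care at 12 months | MCCP at 12 months | Difference | Share of early difference |
|---|---|---|---|---|
| 0 | 7.0% | 17.0% | 10.0 points | 100% |
| 5% | 0.07 + 0.93 × 0.05 = 11.7% | 0.17 + 0.83 × 0.05 = 21.2% | 9.5 points | 95% |
| 10% | 0.07 + 0.93 × 0.10 = 16.3% | 0.17 + 0.83 × 0.10 = 25.3% | 9.0 points | 90% |
| 20% | 0.07 + 0.93 × 0.20 = 25.6% | 0.17 + 0.83 × 0.20 = 33.6% | 8.0 points | 80% |

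The share retained, 1 − h, does not depend on the borrowed rates. A count limited to first events in months 6 to 12 among patients without one by month 6 gives h in both arms. The difference is then 0, as it should be when there is no later effect.

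**Reading B: starters among those referred.** Assume 10% (usual care) and 20% (MCCP) are referred by month 6. A fraction g of the rest is referred later in both arms, and half of the later referrals start.

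- *Early conversion differs, 50% versus 70%.* With g = 0 the 12-month difference is 20 points.
  - With g = 5%, usual care is (0.10 × 0.5 + 0.045 × 0.5)/0.145 = 50.0%. MCCP is (0.20 × 0.7 + 0.04 × 0.5)/0.24 = 66.7%. The difference is 16.7 points.
  - With g = 10%, usual care is again 50.0%. MCCP is (0.20 × 0.7 + 0.08 × 0.5)/0.28 = 64.3%. The difference is 14.3 points.
- *Early conversion equal, 50% in both arms.* The 12-month difference is 0 for every g, although twice as many MCCP patients were referred.

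So on reading B an early difference in conversion carries forward, diluted by later referrals, and a difference in referral alone does not.

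**Would counting any attendance in months 6 to 12 avoid this?** Not fully. Suppose a share r of patients seen by month 6 return in months 6 to 12, and 3% of the rest have a first visit, equally in both arms. The difference is (pT − pC)(r − 0.03). With 7% versus 17%, r = 30% gives 7.59% − 4.89% = 2.7 points, and r = 80% gives 16.09% − 8.39% = 7.7 points. Early linkage reappears through return visits.

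**The case against.** The strongest reply is that nothing is hidden. Table 2 says that Maintenance is examined through outcomes at 12 months, and items 3 and 4 are plainly worded as within 12 months. A cumulative figure has a use: it captures a patient referred before month 6 whose first visit comes after it. Items 1 and 2 isolate months 6 to 12 for referrals, and a reader sees all four measures. The items may also have been meant to follow the newly referred patients of items 1 and 2. Exact windows and denominators may be set in the full protocol or analysis plan, which is not shown.

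Most of this stands, and it limits the weight of the point. It does not remove it: the printed wording of items 3 and 4 has no lower bound, nothing links them to items 1 and 2, and a cumulative proportion does not separate an effect that lasted from one that ended.

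A reader might go further and infer that a vanished effect would usually be declared maintained. A simulation with 8 PACTs per arm, 7% versus 17% at month 6, an equal later event probability of 0 to 7%, ICC 0.02 to 0.04 and 200 to 1000 patients per PACT does favour MCCP in about 59% to 98% of trials on the cumulative measure. The documents do not support that as a property of this trial. The rates belong to the primary outcome, and the denominator is taken to be all patients. On reading B, with referral of 7% versus 17% and equal 50% conversion, the same kind of simulation favours MCCP in only about 2% to 3% of trials, close to the nominal 2.5%. Table 2 also sets no test or threshold by which items 3 and 4 alone would declare maintenance.

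**Conclusion.** The point holds in a limited form. As worded, items 3 and 4 re-count the month 0 to 6 events of Effectiveness items 4 and 5, so by themselves they cannot show that an effect was sustained beyond month 6. On an all-patient denominator, 1 − h of the early difference remains at 12 months with no later effect, which is 80% to 100% for h from 20% down to 0. On a referred-patient denominator, only an early difference in conversion carries over. The wording does not settle which denominator applies, and no start or visit rates are given, so the size in points is illustrative only.

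Severity is minor. These are RE-AIM measures for the summative evaluation; the primary outcome is unaffected, and items 1 and 2 still isolate the later period for referrals.

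**What to change.** 1. Label Maintenance items 3 and 4 as cumulative 12-month outcomes and do not use them as evidence of maintenance.
2. For Maintenance, report first programme starts and first hepatology visits in months 6 to 12 among patients without one by month 6. State the denominator, define it the same way in both arms, use the same GLIMMIX model, and show the result next to the cumulative figure.
3. If attendance in months 6 to 12 by patients linked earlier is also reported, call it continued engagement, because it partly reflects early linkage.

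The cost is a wording change in Table 2 and one date-restricted query of CDW data; Table 1 already lists weight-loss enrolment and hepatology clinic visits at 6 and 12 months. There are two drawbacks. The maintenance result may look less favourable than the cumulative one. The first-event measure also leaves out patients who had already started by month 6, and more of these may be in one arm than the other, so it has to be read together with the cumulative figure.
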